## Abstract

**Background:**

More than 60% of stroke survivors experience residual deficits of the paretic upper limb/hand. Standard rehabilitation generates modest gains. Stimulation delivered to the surviving Primary Motor Cortex in the stroke-affected hemisphere has been considered a promising adjunct. However, recent trials challenge its advantage. We discuss our pilot clinical trial that aims to address factors implicated in divergent success of the approach. We assess safety, feasibility and efficacy of targeting an alternate locus during rehabilitation- the premotor cortex. In anticipating variance across patients, we measure neural markers differentiating response from non-response.

**Methods/Design:**

In a randomized, sham-controlled, double-blinded pilot clinical study, patients with chronic stroke (n = 20) are assigned to receive transcranial direct current stimulation delivered to the premotor cortex or sham during rehabilitation of the paretic arm/hand. Patients receive the designated intervention for 30 min, twice a day for 3 days a week for 5 weeks. We assess hand function and patients’ reports of use of paretic hand. A general linear mixed methods model will analyze changes from pre- to post-intervention. Responders and non-responders will be compared upon baseline level of function, and neural substrates, including function and integrity of output tracts, bi-hemispheric balance, and lesion profile. Incidence of adverse events will be compared using Fisher’s Exact test, while rigor of blinding will be assessed with Chi-square analysis to ascertain feasibility.

**Discussion:**

Variable success of cortical stimulation in rehabilitation can be related to gaps in theoretical basis and clinical investigation. Given that most patients with severe deficits have damage to the primary motor cortex or its output pathways, it would be futile to target stimulation to this site. We suggest targeting premotor cortex because it contributes substantially to descending output, a role that is amplified with greater damage to the motor cortex. With regards to clinical investigation, paired cortical stimulation in rehabilitation has been compared to rehabilitation alone in unblinded trials or to unconvincing sham conditions. Transcranial direct current stimulation, a noninvasive technique of brain stimulation, which offers a more effective placebo and has a favorable safety-feasibility profile, may improve scientific rigor. Neural markers of response would help inform patient selection for future clinical trials so we can address limitations of recent negative studies.

**Trial registration:**

NCT01539096

## Background

### Arm/hand deficits post-stroke: evidence regarding adjunctive cortical stimulation

Stroke is the leading cause of long-term disability in adults
[1]. More than 60% of survivors experience residual deficits of the paretic upper limb
[2,3], where standard rehabilitation generates only modest gains
[4]. A promising new approach involves delivering adjunctive stimulation to the brain. Early studies show that electrical stimulation delivered to the surviving primary motor cortex (M1) in the stroke-affected hemisphere in conjunction with rehabilitation facilitates outcomes of the paretic extremity
[5-14]. Translational models suggest the effect is synergistic and emerges from augmented activity within targeted, residual M1
[5-7]. Despite its preliminary success, recent clinical trials have failed to witness an advantage of the paired approach in comparison to rehabilitation delivered alone
[15-19]. Gaps in the theoretical basis and variability of experimental design are implicated
[4,19].

### Gaps in the theoretical basis and variability in experimental design

Studies have invariably targeted M1 in the stroke-affected hemisphere
[8-10,15]. Given that M1 and its output pathways are spared only in few patients with focal lesions
[20,21], targeting M1 may be ineffective across most. It is thus important to deviate from the classical strategy of stimulating M1 while still realizing that effectiveness may vary depending upon who is enrolled. Well recovered patients demonstrate promise of additive stimulation
[14,22], but disappointing results are observed in patients with severe impairments
[16,18]. The obvious theoretical questions remain - are the effects of adjuvant cortical stimulation favorable for some versus others, and why?

The clinical utility of paired stimulation in rehabilitation is also marred by variability in design. The paired approach has been compared to either rehabilitation alone in unblinded trials
[8-10] or to unconvincing sham stimulation
[16,23] or to no control conditions at all
[24,25]. Approaches of stimulation are extremely variable too, with little information about why one method may have greater utility than another. Invasive techniques (intracranial stimulation of residual M1) carry serious postsurgical risks
[8], but even noninvasive methods (delivered from over the scalp and skull), such as repetitive transcranial magnetic stimulation, rTMS, may induce acute seizures
[26]. Plus, rTMS is non-portable, and impractical to apply in chronic rehabilitation
[27], unlike invasive stimulation
[8-10]. Modes of stimulation are distinct too, with some facilitating activity of stroke-affected hemisphere, and others downregulating that of the unaffected
[28].

Rehabilitation strategies are inconsistent; some groups employ laboratory-based training paradigms
[13,14,22,29], whereas others use standard
[8-10,16,17,23-25,30] or newer methods of rehabilitation
[12,18,31]. It is critical to understand that the type of training that is combined with stimulation determines how generalizable the benefits would be. Improvements are specific for tasks that are strategically paired with stimulation
[7,29,32], thus, choosing a rehabilitative intervention/paradigm that is applicable across most activities of daily living would indeed be more meaningful. Additionally, duration is important because singular sessions of paired stimulation and training tend to be positive
[13,14] and hence, popular, but they may inflate and contort the clinical advantage that is truly offered by stimulation.

### Rationale for our approach

In addressing theoretical gaps in the present literature, we propose that premotor cortex (PMC) could serve as an alternate locus in the stroke-affected hemisphere. As a higher-order motor region, it contributes substantially (approximately 60%) and independently to descending motor tracts, plays a superior role in dexterity
[33-35], and contributes more strongly with increasing damage to M1
[36,37]. Descending motor output from PMC has as strong a predictive power in prognosticating recovery as output from M1
[38,39]. However, in anticipating that effects of stimulation can vary across patients, we propose to assess pathologic and neural markers of individual recovery
[4,19] to inform design of future trials.

Since variability in design, choice of stimulation and its mode, and type of rehabilitative strategy have impacted interpretation of the utility of paired stimulation in stroke rehabilitation, here, we suggest design-related modifications for upcoming trials. When selecting between methods of cortical stimulation, an alternative non-invasive technique may involve transcranial direct current stimulation (tDCS), which with passage of low-level current alters cortical excitability. tDCS may provide a better safety-feasibility ratio than intracranial and rTMS methods because it induces minimal risks, offers effective placebo and is low cost and easy to administer in patients with chronic conditions with concurrent therapies
[14,18,22,40]. With respect to rehabilitation protocols, adopting a paradigm that is standardized yet customizable to patients’ goals and objectives would be more effective in promoting generalizability; an example is modified constraint-induced movement therapy (CIMT)
[41], involving use of paretic limb in patient-specific tasks simulating activities of daily living during constraint of the unaffected limb. CIMT may also be effective as a paired rehabilitation technique because it is shown to facilitate activity in targeted, residual M1 and restore inter-hemispheric balance
[41]; delivering adjunctive tDCS could then amplify its neural basis and effectiveness
[12]. Long-term rather than short-term pairing with rehabilitation may carry greater utility. This is because the effects of short-term tDCS are transient
[42], but longer staggered paradigms generate greater retention
[42,43]. Incorporating extended treatment paradigms
[16-18,24,44] would also be important for making decisions about long-term clinical relevance
[13,14,22,29,45] of paired cortical stimulation and rehabilitation.

### Objectives and hypotheses

In line with our rationale, the objectives of the present pilot clinical study are to: 1) examine the safety, feasibility and effectiveness of CIMT paired with tDCS targeting PMC, versus CIMT delivered alone in alleviating impairments of the paretic hand in patients with chronic stroke; and 2) assess neural markers associated with response to paired paradigm versus CIMT alone.

We hypothesize that the paired approach involving stimulation of PMC in the stroke-affected hemisphere will be more effective than CIMT in improving hand function in chronic stroke. The paired approach will facilitate the individual’s specific neural substrates of recovery and will be safe to employ throughout the length of the study.

## Methods

### Study design

We use a pilot, randomized, sham-controlled, double-blind clinical study design. Twenty patients are being randomly assigned to PMC tDCS plus CIMT or sham tDCS plus CIMT groups. All outcomes are collected at pretest and at post-test after 5 weeks of intervention. At 3-month follow up, outcomes of hand function are collected to examine retention.

### Participants and recruitment

We are enrolling patients with chronic stroke with mild-to-moderate impairments in upper limb function
[46,47], who fulfill the following prerequisites:

### Inclusion and exclusion criteria

The inclusion criteria are: age ≥21 years; chronic phase of recovery (>6 months) after first-ever stroke up to 20 years post-stroke; ability to extend fingers or thumb or wrist ≥10° and chief complaint of inadequate ability to use the paretic hand compared to its use prior to a single (ischemic or hemorrhagic) stroke.

The exclusionary criteria relate to contraindications of cortical stimulation
[48,49] and imaging
[36,37]. These include: cardiac pacemaker; metallic implant in the head; seizure disorder; medication-resistant epilepsy in a first-degree relative; use of any neuro- or psycho-active medications as published in recommendations
[48]; history of fainting spells of undetermined etiology; pregnancy; implanted pumps/stimulators/shunts; any other neurological condition affecting sensorimotor systems, such as brain tumor, dementia, or substance abuse; severe cognitive deficits (mini-mental state exam score
[50] <18); ongoing/recent (within 2 months) rehabilitation for upper limb.

### Recruitment

This is a single-center pilot clinical study. Patients with chronic stroke are being recruited from nine area hospitals within the Cleveland Clinic health system through outpatient and community-based stroke programs, referrals from providers, medical chart review, liaison with local support groups, and spontaneous demand through newspaper, radio and website advertisements.

### Ethics, consent, study organization and registration

The study is being conducted in agreement with the principles of the Declaration of Helsinki, and with the guidelines of Good Clinical Practice (GCP) of the International Conference on Harmonization of Technical Requirements for Registration of Pharmaceuticals for Human Use (ICH). The study protocol has been approved by the local and independent Ethics Committee of the Cleveland Clinic (Institutional Review Board). The study is also registered as a pilot clinical trial on clinicaltrials.gov (NCT01539096). Extramural funding for the present study is provided by the National Institutes of Health (NIH) for EP.

During the consent process, the investigator explains the benefits and risks of participation in the study and provides an informed consent form approved by the Institutional Review Board. To gauge whether subjects have sufficiently understood the study processes so as to make an informed decision, the investigator probes by asking open-ended questions about details contained in the consent form. Only patients who respond correctly and provide written informed consent by signing the consent document are enrolled in the study. Results will be published only with de-identified data.

### Initial screening

Patients are initially screened by telephone, followed by thorough chart review. The physical therapist, principal investigator and study coordinator evaluate subjects, who provide written informed consent in person, to ensure eligibility. Diagnosis and eligibility are confirmed at screening by a neurologist. Screening for neuroimaging and brain stimulation is repeated at each of these levels.

### Study assessments

Following confirmation of eligibility, the pretest is scheduled over 2 days, and involves evaluation of upper limb function and neural markers of change. Post-test, following 5 weeks of the assigned intervention, is similar to the pretest.

Outcomes of hand function: the detailed timeline is presented in Figure 
1. Our primary outcome of hand function is the upper extremity Fugl-Meyer (UEFM) assessment, which measures impairments of the upper limb/hand
[51]. It is commonly used in studies pairing cortical stimulation with rehabilitation
[8-10]. It includes 33 items that provide a gross indication of overall functional status of an individual. It is rated on an ordinal scale (0 to 2, maximum score 66) by an investigator
[51].

**Figure 1 F1:**
[figure not shown]
**Overview of study procedures.** CIMT, constraint-induced movement therapy; tDCS, transcranial direct current stimulation; MRI, magnetic resonance imaging.

Secondary outcomes of function include: 1) the motor activity log
[47], which is a self-report assessment of the patient’s own perception of degree and quality of use of their affected hand in daily activities; 2) the Action Research arm test, which is a performance-oriented test that rates function across grasp, grip, pinch, and gross movement
[52]; 3) the nine-hole peg test, which is a performance-oriented test of dexterity measuring time-to-place individual pegs consecutively into spaces and removing them as promptly as possible
[53]; 4) isometric finger-abduction strength measured as force exerted during maximum isometric abduction; and 5) spasticity of finger and wrist flexors measured with the modified Ashworth scale
[54], which ranges from 0 (no change in muscle tone upon quick stretch) to 4 (most severe spasticity, where the hand is rigid in flexion). All outcomes of hand function are repeated at a 3-month follow-up assessment.

### Markers of neural recovery

Neuroimaging and tests of cortical neurophysiology are being conducted at pretest and at post-test to identify predictors and correlates of response, compare which substrates are adaptive in one individual versus another, and discern the potential underlying reason for variance.

#### Structural neuroimaging

Predictors of response: diffusion tensor imaging defines the structural patency of white matter tracts
[55]. Using this method, we evaluate the integrity of corticospinal tracts, which are considered most critical to dexterity
[56]. We anticipate that PMC-based tracts will be more predictive of recovery with tDCS than those emerging from M1.

#### Functional neuroimaging

Mechanisms of response: functional neuroimaging is the most important assay to measure changes in the brain occurring in recovery in stroke. By measuring changes in perfusion or blood oxygenation during movement of the paretic hand, one can infer the association of activity of a region with its role in dexterity. Functional neuroimaging, such as functional MRI (fMRI), has demonstrated that damage due to stroke downregulates activity in stroke-affected versus intact hemispheres. As recovery occurs, the balance in activity (as seen using fMRI) between bilateral hemispheres, returns
[37,41]. We are exploring whether delivering tDCS to PMC in the stroke-affected hemisphere helps restore this balance. Another form of functional neuroimaging, called resting-state fMRI
[57], is critical in identifying how, over the course of stroke recovery, functional connectivity (fc) evolves between widespread networks
[58]. We investigate whether fc is strengthened, particularly between PMC and M1, with application of tDCS in CIMT.

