#### Neurophysiology

Substrates of response: transcranial magnetic stimulation (TMS) noninvasively measures cortical and corticospinal neurophysiology
[59]. In the present pilot trial, TMS defines efficiency of conduction via residual corticospinal tracts
[56], the structural integrity of which is outlined with diffusion tensor imaging. TMS also measures conduction between both hemispheres relayed via transcallosal pathways; this conduction is normally inhibitory, that is, one hemisphere exerts inhibition upon another, and that in return exerts counter-inhibition. In stroke, balance of such inhibition is disrupted. Whereas inhibition from the intact stroke-affected hemisphere is exaggerated, that in the opposite direction is diminished
[60]. We explore whether tDCS delivered to PMC in the stroke-affected hemisphere improves the efficiency of corticospinal conduction and helps rebalance inhibition exerted between the intact and stroke-affected hemispheres.

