#### tDCS

The tDCS of anodal polarity is delivered to PMC in the stroke-affected hemisphere to potentially raise its activity
[49]: it is delivered using a constant current battery-driven (9-V) stimulator (Soterix, NY, New York, USA) connected to conductive rubber electrodes (5 × 7 cm^2^) placed in saline-soaked sponges
[61]. The anodal electrode is placed on the scalp site corresponding to PMC
[34,61], guided by MRI-based stereotaxy. Specifically, the center of the anode is 3 cm anterior to the locus in the stroke-affected hemisphere that evokes the best and most consistent responses with TMS in a muscle of the paretic hand
[61]. The reference (cathodal) electrode is placed above the contralateral orbit. Electrodes are secured using Velcro bands. Direct current is delivered at a dose of 1 mA during rehabilitation in patients in the tDCS plus CIMT group. For patients in the sham tDCS plus CIMT group, the 1 mA current is delivered transiently (30 to 60 seconds) at outset, and then slowly turned off after habituation. For all patients, the current is ramped up slowly at the onset of intervention to minimize excessive tingling and maintain blinding. This is a valid method for placebo as patients receiving tDCS become habituated to its sensation within a short time
[62].

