To assess neural substrates of recovery, both groups will be compared for change in inter-hemispheric balance (fMRI), fc and transcallosal inhibition and corticospinal conduction (TMS) from pretest to post-test. To understand whether effects of interventions vary across patients and factors explaining such variance, an ideal method would have involved identifying clinical, pathologic and neural factors that would predict the change in UEFM. However, since the statistical power of the study may be inadequate to pursue this analysis, we will follow an alternative method. Patients who achieve ≥3.5 gain in the UEFM score (criterion of clinical improvement defined in a previous clinical trial of invasive cortical stimulation)
[8] after 5 weeks of the intervention would be called responders. We will investigate whether the proportion of responders versus nonresponders includes a greater majority of patients from the tDCS group (Chi-square analysis). More importantly, we will compare clinical, pathologic and neural indicators between responders and nonresponders (independent samples *t*-test). These will include: baseline UEFM, location of disease (Oxford Stroke classification: total anterior circulation or partial anterior circulation or lacunar strokes)
[66], residual function and integrity of corticospinal tracts on the stroke-affected side measured with TMS and diffusion tensor imaging respectively.

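### The only task-fMRI comparison listed is between-hemisphere balance, which does not by itself show whether the stimulated side rose or the intact side fell

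*Protocol article*

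**What the plan says.** Under tDCS, the Protocol article gives the purpose of the stimulation: "The tDCS of anodal polarity is delivered to PMC in the stroke-affected hemisphere to potentially raise its activity".

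Under Functional neuroimaging, activity is recorded while the paretic hand moves, but the outcome described is relative: "As recovery occurs, the balance in activity (as seen using fMRI) between bilateral hemispheres, returns". The question asked of the trial follows from it: "We are exploring whether delivering tDCS to PMC in the stroke-affected hemisphere helps restore this balance". The same section plans one measure that involves the target, from resting-state fMRI: "We investigate whether fc is strengthened, particularly between PMC and M1, with application of tDCS in CIMT".

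Under Neurophysiology, TMS is used to ask whether stimulation improves corticospinal conduction and "helps rebalance inhibition exerted between the intact and stroke-affected hemispheres".

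Under Statistical and data analyses, the neural comparisons between arms are listed: "both groups will be compared for change in inter-hemispheric balance (fMRI), fc and transcallosal inhibition and corticospinal conduction (TMS) from pretest to post-test". Task activity of the stimulated PMC, or of either hemisphere separately, is not in that list.

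**The concern.** The stated action of the treatment is on one side and one region. The listed task-fMRI outcome is a contrast between two sides. The article itself treats the two ways of changing that contrast as different: the section on gaps in the theoretical basis describes modes of stimulation that facilitate the affected hemisphere as distinct from modes that downregulate the unaffected one. A balance measure merges the two.

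The Discussion names the novel target as the first strength of the study. If balance shifts more in the tDCS arm, it would be natural to report that the premotor cortex was facilitated, when the change may lie wholly on the intact side. If balance does not shift, changes on the two sides may have cancelled. In both cases the next trial would learn less about the target than the scans could tell it.

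A smaller, separate point is that the arms are to be compared on change from pretest to post-test. Each measure has a pretest value that could serve as a covariate, which is usually the more precise comparison.

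**Working it through.** **Inputs.** The article gives no formula or region for the balance measure, and no pre-post correlation for any neural marker. Everything numerical below is therefore an illustration on assumed values. Let A be activity on the stroke-affected side and B activity on the intact side. Take A = 0.8 and B = 1.2 before treatment, in line with the statement under Functional neuroimaging that stroke lowers activity on the affected side relative to the intact side.

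**1. Laterality index, (A - B)/(A + B).**
- Before: (0.8 - 1.2)/(0.8 + 1.2) = -0.4/2.0 = -0.200.
- Affected side up 25%, intact side unchanged: (1.0 - 1.2)/(1.0 + 1.2) = -0.2/2.2 = -0.091.
- Intact side divided by 1.25 (down 20%), affected side unchanged: (0.8 - 0.96)/(0.8 + 0.96) = -0.16/1.76 = -0.091.
- Both sides down, to 0.70 and 0.84: (0.70 - 0.84)/(0.70 + 0.84) = -0.14/1.54 = -0.091.

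All three show the same improvement in balance. In the third, the stimulated side has fallen.

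**2. How far this depends on the index.**
- Ratio A/B: 0.8/1.2 = 0.667 before; 1.0/1.2, 0.8/0.96 and 0.70/0.84 are each 0.833 after. Again identical.
- Difference A - B: -0.40 before. Raising A by 0.2 gives 1.0 - 1.2 = -0.20, and lowering B by 0.2 gives 0.8 - 1.0 = -0.20. Identical.
- Laterality index with the same additive changes of 0.2: -0.2/2.2 = -0.091 (A up) and -0.2/1.8 = -0.111 (B down). Close, but not equal.

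Exact equality therefore needs reciprocal proportional changes on a ratio-type index, or equal additive changes on a difference. What holds on every form tested is weaker and sufficient: the value of the balance does not identify the side that moved.

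**3. Whether another listed comparison fills the gap.**
- Resting connectivity, particularly PMC to M1, involves the target but measures coupling, not level of activity.
- Corticospinal conduction is not a balance measure, but it is not PMC activity.
- Transcallosal inhibition is described in two directions. If it is summarised as a rebalancing, it carries the same ambiguity as the fMRI balance.
- The Discussion foresees regional fMRI readings in patients with little response, but of alternative areas, not the stimulated one.

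**4. Plain change against baseline adjustment.** With equal variance s² at both visits and pre-post correlation rho, a comparison of change has variance proportional to 2s²(1 - rho). A comparison of post-test values adjusted for pretest has variance proportional to s²(1 - rho²). The ratio is (1 - rho²)/(2(1 - rho)) = (1 + rho)/2.

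| rho (assumed) | ratio | variance saved |
|---|---|---|
| 0.3 | 0.65 | 35% |
| 0.5 | 0.75 | 25% |
| 0.7 | 0.85 | 15% |

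These ratios ignore the small cost of estimating the slope with 10 patients per arm.

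**The case against.** The strongest reply is that the measure answers the question asked. The article asks about balance, not about PMC level. Its rationale says that constraint therapy restores inter-hemispheric balance and that tDCS could amplify this. Under Neurophysiology, inhibition from the intact hemisphere is described as exaggerated after stroke, so a fall in intact-side influence may itself be part of the recovery sought. The phrase about raising activity explains the choice of polarity and is not declared as an outcome, and nowhere does the article say that a balance shift will be read as PMC facilitation. All this is fair. It means that balance is a legitimate outcome to keep. It does not make balance informative about the target.

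A second reply is that this is a condensed article. Index formula, regions of interest and reporting of components commonly sit in the full protocol or analysis plan, and any balance measure requires each side to be estimated first. This stands. A reader might infer that PMC activity will not be analysed at all, or that the plan cannot tell whether the target was raised. The article does not support that: it shows only which comparisons are listed, and a balance computed within PMC is not excluded. Such an index would still be relative, however.

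A third reply limits what the remedy can achieve. Imaging is at pretest and post-test, while current flows during the therapy sessions. Post-test activity reflects lasting change after five weeks of training, not engagement of the cortex during stimulation. With 10 patients per arm, a null result for PMC activity would not show that PMC was not raised. This also stands, so a reader should not expect the added measures to separate a target that was not engaged from one that was engaged without benefit.

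Finally, comparing change does not strictly rule out a baseline-adjusted model. That is so, and the point on the covariate is a request to fix the better choice, not a correction of an error.

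**Conclusion.** The point holds in a limited form. As listed, the task-fMRI comparison between arms is a relative quantity and does not by itself show whether the stimulated side rose or the intact side fell, although raising the stroke-affected PMC is the stated purpose of the treatment. Resting PMC-M1 connectivity is relevant to the target but does not supply the missing measure.

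A reader might infer that the balance always shifts equally under the two mechanisms. That depends on the index, which is not given, and on how the changes are matched. On the laterality index, additive changes of 0.2 gave -0.091 and -0.111, not the same value.

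The consequence is confined to exploratory mechanism analyses in a pilot of 20 patients. The primary Fugl-Meyer comparison, safety and feasibility are untouched. The gain from baseline adjustment is 15% to 35% of variance for rho between 0.7 and 0.3, assuming equal variances at the two visits; the documents give no value of rho.

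**What to change.** 1. Keep the balance measure. Beside it, report between-arm estimates with confidence intervals for paretic-hand task activity in the stroke-affected PMC, for task activity in each hemisphere, and for each direction of transcallosal inhibition. Label all of them exploratory.
2. For each neural marker, compare arms on the post-test value with the pretest value as covariate, in place of plain change.
3. State that a shift in balance will be attributed to facilitation of PMC only if the measure from the stroke-affected side supports it.
4. State two limits with the results: post-test imaging shows lasting change after five weeks and not engagement during stimulation, and a null result at 10 per arm does not show that PMC activity was not raised.

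The cost is wording and a few more exploratory estimates. No new scans or visits are needed, because both hemispheres must already be measured to form a balance and the pretest values are already collected.
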